### Phase II: action

In the action phase participants try to achieve their behavioral goal, by performing the specific actions that they have planned. The important determinants in this phase are awareness of the progression toward a successful behavior change and self-efficacy. Participants are asked to monitor every day for themselves whether they achieved their goal (i.e. monitoring [30]) and which difficult situations they encountered (i.e. prompting identification of barriers [30]). This information can be used by the participants as feedback on the achievement of the goals and plan, and is used as input for the evaluation phase.

### Phase III: evaluation

#### **
*Awareness of the progression of the behavior change*
**

The first method to target awareness in the evaluation phase is monitoring the progression of the target behavior. Participants can state for each day of the past week whether or not they achieved their behavioral goal (i.e. monitoring progression of behavior change/prompt review of behavioral goals [30]). Based on this monitoring, tailored feedback on performance [30,63,64] is provided. For fruit and vegetable consumption, participants also report their fruit or vegetable consumption in the past week. Fruit and vegetable consumption is then compared with the consumption during the previous visit to the intervention and participants receive feedback on their progress in fruit and vegetable consumption. The snack and fat module did not include monitoring of intake, because the assessment questionnaires were quite long.

#### **
*Attitude*
**

A decisional balance is used to target attitude in the evaluation phase. Participants who indicate they have not achieved their behavioral goal because they were not motivated are stimulated to make a decisional balance by specifying, in provided text boxes, the advantages and disadvantages of changing the target behavior. Subsequently, an overview of this balance is provided and participants are stimulated to review the balance. After seeing their decisional balance, participants can indicate whether they are motivated to make a second attempt or whether they want to choose another target behavior.

#### **
*Self-efficacy*
**

To target self-efficacy in the evaluation phase, coping planning is used [65]. Participants who indicate they have not achieved their behavioral goal because of circumstances can select which circumstances hindered them to perform their intended actions from a predefined list (e.g. ‘I had a very strong desire to eat something else’) or describe a situation via an open-ended question. Subsequently participants are stimulated to make a plan to overcome the same situation the next time (i.e. coping planning). Coping planning is provided in an open-ended format, in which participants can state their own solution to overcome the difficult situation.

In addition, all participants can state which difficult situations they expect in the following weeks. Participants can choose a situation from a predefined list (e.g. ‘When the fruit I want to eat is not available’) or specify an expected situation via an open-ended question, and are subsequently stimulated to make a plan to overcome this situation (i.e. coping planning, provided in an open-ended format).

Next, participants are asked whether they are confident of achieving their goal in the next time period. When they are not confident, they have the opportunity to lower their goal in order to make it more feasible. When they are confident they have the opportunity to increase their goal in order to make it more challenging.

The last method to target self-efficacy in the evaluation phase is providing instructions [30] and information about how participants can maintain their new behavior. Participants are instructed to follow a specific sequence of actions, for example: ‘Monitor your fruit consumption’, ‘Make a plan for a new difficult situation’, and ‘Adapt plans that are not effective enough’. Also, instructions on what to do when one relapses to old habits and some practical suggestions on how to maintain the new behavior are provided, such as ‘Make sure you always have fruit available at home’.

### Step 4: development of the online tailored intervention

The web-based, computer-tailored intervention we developed is called ‘Bewust eten, hoe doe je dat?’ (‘Conscious eating, how do you do it?’) and consists of four modules: fruit, vegetables, high-energy snacks and (saturated) fat. The methods, as described in the previous part, are incorporated into two versions of the intervention. One version, the basic version, is only targeted at the individual cognitions and volitional and self-regulation processes, and therefore only includes the methods on knowledge, awareness, attitude and self-efficacy. The other version, the plus version, additionally targets the environmental factors and therefore also includes methods on the availability and accessibility of healthy food products in the home environment and the perception of availability and price of healthy food products in the supermarket. The technical development, involvement of the target group and the outline and sequence of the final intervention are described in more detail below.

### Development of the online tailored intervention

The web-based, computer-tailored intervention is developed using the TailorBuilder software (OSE, the Netherlands), which is suitable for generating tailored feedback based on assessment questionnaires, tailoring algorithms and feedback messages. The intervention is delivered via a website (see Figure 1) where participants can log in with their personal codes.

**Figure 1 F1:**
[figure not shown]
Print screen of the homepage of the intervention.

The individual feedback on the intake of fruit, vegetables, high-energy snacks and fat is based on existing computer-tailored nutrition education interventions [66,67]. The (feedback on) beliefs and barriers included in the intervention are partly based on these interventions, but also new beliefs and barriers are included, based on the input of a consumer panel (see Involving the target group during intervention development).

The environmental information, which consists of the availability and price of selected fruit, vegetables, lower-energy snacks and lower-fat products, is collected via observations in the local supermarkets (n = 58). A research assistant audited the cooperating supermarkets (n = 31) and observed the availability and price of selected products. Subsequently, the observed local supermarket information was incorporated into the computer-tailored intervention. Unfortunately, not all supermarkets agreed with the observations. For the non-cooperating supermarkets (n = 27, of which 23 are affiliates of three large supermarket chains who did not wish to participate), general information on the availability and price of healthy food products in supermarkets is provided to the participants. To keep product prices up to date, supermarket representatives were asked to send price updates every month. Most of the time, however, the research assistant had to re-audit the supermarket to update prices. In addition, information on websites of supermarkets is used to collect information about the availability and price of products and to update the information.

### Involving the target group during intervention development

Representatives of the target group, consisting of high- and low-educated adults aged 20–65 years, were involved during the developmental phase in two ways: via a consumer panel and a pretest.

### Consumer panel

The consumer panel consisted of 55 people from the target group (mean age 51.31 years (SD = 12.43); 63.6% women; 40% low-educated) who were recruited via spreading flyers in low SES neighborhoods and recruiting people in shopping malls.

Members of the consumer panel were contacted multiple times via e-mail or phone. They were asked to provide input on, for example: advantages and disadvantages of the target behaviors; barriers to performing the target behavior; and locations in the home environment to store food products. They were also asked to provide feedback on ideas about the intervention name, appreciation of the recruitment folder and on how we could reach participants for the evaluation study. With the help of the consumer panel we were able to make the intervention fit the target group and to address beliefs and barriers that are salient in the target group.

### Pretest

A first version of both versions of the intervention was pretested in order to identify points for improvement. A total of 44 persons participated in the pretest of the basic version. A qualitative and a quantitative pretest were conducted.

Twelve people (mean age 41.9 years; 75% women; 50% low educated) participated in the qualitative pretest. During this pretest participants worked through the intervention in the presence of a researcher, who stimulated participants to think aloud and asked in-depth questions to check the comprehensibility of the information, such as ‘Can you explain in your own words what you have read?’. Afterwards, participants filled out a short questionnaire to express their appreciation of the intervention and were stimulated to explain their answers. The qualitative pretest was also used to pretest the homepage of the website (see Figure 1); participants were asked to give feedback in terms of attractiveness, clarity and comprehensibility.

Twenty-eight participants (mean age 48 years; 64.29% women; 35.7% low-educated) participated in the quantitative pretest of the basic version of the intervention. Participants worked through the intervention at home and filled out a questionnaire that measured, amongst others, appreciation (e.g. ‘What score do you give this intervention?’), user-friendliness (e.g. ‘This intervention was easy to use’) and comprehensibility (e.g. ‘The information was easy to understand) of the intervention and specific components.

The basic version of the intervention was appreciated quite well (average rating = 7.98 (SD = 1.06)) and the information was rated as useful, interesting, easy to understand, personally relevant and user-friendly. The time it took to work through the intervention was rated as being acceptable. Points for improvement were the attractiveness of the layout and the length of the texts. The texts were too long and participants tended not to read all the texts in their entirety. Therefore, the texts were made shorter and more concise. The less positive rating of the attractiveness of the layout was mostly because the intervention was not pretested in its final layout. After finalizing the layout, different members of the consumer panel rated the new design as being attractive. All participants who were shown the website appreciated the layout of the website and thought it was clear how to log in to the website.

A group of six participants (mean age 46.2 years; 83.33% women; 16.67% low educated) pretested the plus version of the intervention and 15 members of the consumer panel provided feedback on an example of price and availability information for lower-energy snacks. The plus version was scored with a 7.7 (SD = 0.98). The most important results were that the environmental information was seen as being too independent from the other parts of the intervention and therefore it was not clear how it related to the tailored feedback on other determinants. Also, two participants thought the information was too commercial and thought the goal was to show supermarket advertisements. The first comment was solved by incorporating environmental information in the attitude and self-efficacy sections in order to relate it to the other information. To solve the commercial look of the environmental information, we accompanied the information about availability and prices with more textual information in order to explain why this information is relevant.

### Scope and sequence of the intervention

Each module (i.e. fruit, vegetables, high-energy snacks and fat) consists of three sessions of approximately 30 minutes that can be worked through with a two-week interval between each session (taking six weeks in total). All sessions consist of multiple sections in which specific determinants are targeted. A general outline of the intervention is shown in Figure 2. The content and sequence of the sessions are described below. The content and sequence for the modules about vegetables, fruit and high-energy snacks are the same. The module about fat intake, however, does not include the attitude and self-efficacy sections in the first session, in order to limit participant burden, since the assessment of fat intake is quite long.

**Figure 2 F2:**
[figure not shown]
Overview of the sequence of the intervention.

### First session

After receiving their log-in code and password participants can log in to the intervention via a special website (see Figure 1). After reading a short introduction to the intervention participants can choose which target behavior they want to address first.

The first session is aimed at the pre-action phase of self-regulation and starts with increasing knowledge of the target behavior: participants can self-tailor the information by choosing the topics of their interest. The next section is aimed at awareness: participants fill out an assessment questionnaire on the target behavior and receive tailored feedback. When participants already comply with the dietary guidelines, they are provided with the opportunity to choose another target behavior. When they do not comply, they enter the attitude section.

The attitude section is not compulsory; participants who indicate that they think changing the target behavior is important are given the opportunity to skip this section. The attitude section first addresses the advantages and subsequently the disadvantages regarding (changing) the target behavior. Subsequently, self-efficacy is targeted, which is also not compulsory and can be skipped (partly or completely) when participants are already confident that they can change the target behavior. The first part of the self-efficacy section is aimed at barriers and the second part at difficult situations.

The plus version has two extra sections after the self-efficacy section. First, the home environment regarding the target behavior is targeted and subsequently objective information is provided about the availability and price of healthy food products in the supermarket where the participant tends to do his or her shopping.

The first session ends with setting a goal and formulating an implementation intention. After formulating the behavioral goal and implementation intention, an overview of this goal and implementation intention is provided on screen. The goal and implementation intention can be printed and are also saved on the website and can be reviewed when revisiting the website. At the closing page of the first session, participants can choose another target behavior or close the intervention.

After the first session, participants can execute their plan(s) for two weeks in order to achieve their goal(s) (i.e. the action phase). After two weeks, they will be invited by e-mail to return to the intervention for the second session.

### Second session

The second session is aimed at the (short-term) evaluation of the behavior change and starts with targeting the awareness of the behavior change: participants can monitor their goal achievement and receive tailored feedback.

Participants who did achieve their goal on all days are complimented and forwarded to the ‘expected difficult situations’ part. Participants who did not achieve their goal on all days enter either the self-efficacy section to identify encountered difficult situations and to formulate coping plans, or the attitude section to see whether they are still motivated. Participants who indicate that they are not motivated to make a second attempt are forwarded to a page where they can choose another target behavior.

All participants, except participants who are redirected to another target behavior, subsequently enter the expected difficult situations part in which a coping plan is formulated. The last part of the self-efficacy section is aimed at goal setting and provides participants the opportunity to adapt their goal.

The second session ends with an overview of the coping plan(s) and (adapted) goal(s), which can be printed and is also saved on the website. At the closing page of the second session, participants can choose (to evaluate) another target behavior or close the intervention. After the second session, participants again execute their plan(s) for two weeks and will then be invited by e-mail to return to the intervention for the last session.

### Third session

The last session is aimed at long-term maintenance. The first part of the third session is more or less the same as the second session: monitoring the performance in the past week and, if applicable, getting insight into which situations caused failure, and subsequently making coping plans for encountered and expected difficult situations. In addition, the last session provides information and instructions on how participants can maintain their new behavior.

At the closing page of the second session, participants can choose (to evaluate) another target behavior or close the intervention.

### Evaluation plan

The first goal of the evaluation is to examine the efficacy of both versions of the intervention compared to generic nutrition information. It is hypothesized that after exposure to the intervention participants in both intervention conditions will have a higher increase in fruit and vegetable consumption and a higher decrease of high-energy snacks and fat (i.e. the primary outcome measures) compared to the control condition. In addition, it is expected that both versions of the intervention will result in more favorable values for the secondary outcome measures (i.e. self-reported body mass index (BMI), general self-control and general self-regulation) and mediating variables (i.e. motivational determinants, habit, action and coping planning, perceived availability and price of healthy food products in the supermarket and availability of healthy food products at home) compared to the control condition. We will also examine whether there are differences in the efficacy of both versions of the intervention between high- and low-educated adults. We expect that the plus version is more effective for low-educated participants than for high-educated participants, since environmental factors are suggested to be more important among low SES groups (e.g. price [12,47,54]), and to mediate the association between SES and diet [11].

The second goal of the evaluation study is to examine the appreciation and use of the intervention and its components. In addition, the quality of the goals and action plans will be examined.

### Design and procedure

A three-group randomized controlled trial will be conducted to study the effects of both versions of the intervention compared to a control group that will receive generic information about fruit, vegetables, high-energy snacks and fat. The program of the control group also consists of three sessions and will be delivered via the same website as the tailored intervention, ensuring the same layout. Measurements will take place at baseline (T0) and one (T1), four (T2) and nine months post-intervention (T3). Before participation, an informed consent has to be signed and returned by post or e-mail. One month after completing the baseline measurement participants will be randomly assigned to one of the three study groups and participants will have access to their assigned program for two months. Two weeks after each intervention visit e-mail reminders will be sent to prompt returning to the intervention. Invitations to fill out the questionnaires will be sent via e-mail. Two and four weeks after the initial invitation e-mail reminders to fill out the questionnaire will be sent.

When participants fill out all questionnaires, they can win an iPad (of which 20 are allotted) or a gift voucher of 20 euros (of which 500 are allotted). The Medical Ethics Committee of the Erasmus Medical Centre in Rotterdam approved the study protocol (NL35430.078.11/MEC-2010-408). The trial is registered in the Dutch Trial Registry (NTR3396).

### Recruitment of participants

A total of 2,000 adults will be recruited for participation in the study; 900 with a high educational level and 1,100 with a lower educational level. The required number of participants is based on a power calculation, in which 1,400 participants would be sufficient to detect a small intervention effect, with a power of 0.80 and a significance level of p < 0.05. To account for a drop out of 10% of the participants between each measurement, 1,800 participants need to be recruited into the study. To take into account a potentially higher drop out in the lower educational group, we will recruit 200 extra participants in this specific group.

Participants will be recruited in five cities in the south of the Netherlands: Heerlen, Roermond, Venlo, Venray and Weert. The choice to limit the recruitment to these cities was made in order to be able to collect the environmental information needed for the plus version of the intervention. These five cities complied with the inclusion criteria that were defined for cities: having both high and low SES neighborhoods, having at least 25,000 inhabitants, not having too many (small) supermarkets and the municipality should be willing to provide a random selection of home addresses within the cities for recruitment purposes. The main recruitment method will be sending personal letters to randomly selected home addresses, but Facebook advertisements, advertisements in (local) newspapers, local TV and recruitment in shopping malls will also be used as recruitment strategies. Inclusion criteria for the participants are: being between 20 and 65 years of age, having a sufficient understanding of the Dutch language (in reading and writing) and having access to a computer that is connected to the Internet. Exclusion criteria are: being on a diet prescribed by a physician or dietician, having a medical condition that implies restrictions in eating behavior (e.g. CVD or bowel disease) and not willing to sign an informed consent.

### Measurements

Online questionnaires will be used to collect self-reported data on the primary and secondary outcome measures. In addition, the potential mediating variables will be assessed, to be able to investigate the mediating pathways of the intervention effects. A process evaluation will also be conducted to assess appreciation and use of the intervention and the various components. Process measures will be incorporated in the first follow-up questionnaire and will contain questions on perceived attractiveness, user-friendliness, comprehensiveness, usability and perceived personal relevance. Also the appreciation of the environmental feedback and the goal setting and action planning tools will be measured. The use of specific intervention components and the number of visits to the intervention will be measured objectively via web-server registrations. Figure 3 provides an overview of the variables measured at each time point.

**Figure 3 F3:**
[figure not shown]
Overview of the procedure of the evaluation study and measurements.

### Statistical analyses

Repeated measures analyses will be conducted to study differences between the three study groups in changes in the food intake measures (i.e. main effects). Additional analyses will be conducted on secondary and mediating outcome measures. Since five cities were included in this study we will adjust for place of residence by including this variable as a covariate in the analyses. Because people with unfavorable diets probably profit more from the intervention, the efficacy of the intervention will also be assessed among subgroups that do not meet recommended intake levels for each target behavior at baseline. Interaction with educational level will be explored to study whether effects of the intervention differ according to educational level (i.e. interaction effects). To gain insight into the pathways of change, mediation of the intervention effects through the potential mediating variables will be examined with the joint significance test [68]. Descriptive analyses and (multiple) linear and logistic regressions will be conducted to study the appreciation of the intervention, the use of different components and the quality of goals and action plans.

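### The primary comparison is a difference in changes with no stated adjustment for baseline intake, which gives up precision that could be had at no cost

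*Protocol article*

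**What the plan says.** The protocol article describes the primary analysis in the Statistical analyses section: "Repeated measures analyses will be conducted to study differences between the three study groups in changes in the food intake measures". The hypothesis in the Evaluation plan has the same form: a larger rise in fruit and vegetable intake and a larger fall in snack and fat intake than under control.

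One covariate is named: "we will adjust for place of residence by including this variable as a covariate in the analyses". Baseline intake has two roles. It is the starting point of the change, and it defines subgroups: "the efficacy of the intervention will also be assessed among subgroups that do not meet recommended intake levels for each target behavior at baseline". Education appears as an effect modifier: "Interaction with educational level will be explored to study whether effects of the intervention differ according to educational level".

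Under Design and procedure, T0 precedes allocation: "One month after completing the baseline measurement participants will be randomly assigned to one of the three study groups". Three follow-ups come after it, at one, four and nine months post-intervention. Under Recruitment of participants, "1,400 participants would be sufficient to detect a small intervention effect, with a power of 0.80 and a significance level of p < 0.05", with 10% loss planned between successive measurements and possibly more in the lower-educated group. The article names neither the type of repeated measures model nor its estimation method.

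**The concern.** A difference in changes subtracts the whole baseline value, whatever the correlation between baseline and follow-up. Regression on baseline subtracts only the part that predicts follow-up. Under randomisation both aim at the same effect, but subtraction carries extra baseline noise unless r is close to 1.

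A value close to 1 looks unlikely here, although the article gives no figure. Intake is self-reported by online questionnaire and T0 is taken a month before allocation. If the post-intervention months run from the end of the two-month access period, the follow-ups fall about 1+2+1 = 4, 1+2+4 = 7 and 1+2+9 = 12 months after T0.

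At stake is precision on all four primary outcomes, in a trial sized for a small effect and in a field where the article's Background says that effects are often small.

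**Working it through.** **Inputs.** From the article: 1,400 analysed, three groups, power 0.80, significance level 0.05, and 10% loss between measurements. Assumed: equal allocation (1,400/3 ≈ 467 per arm), a two-sided test, equal variance at baseline and follow-up (set to 1), and r from 0.3 to 0.8.

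**The plan's own figure.** The 1,400 cannot be reproduced uniquely, because the small effect is given no value. At 0.2 SD, the two-group formula with SD 1 gives 393 per arm, or 3 × 393 = 1,179. Read the other way, 467 per arm detects (1.96 + 0.84) × √(2/467) = 0.183 SD.

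**Variance per participant, single follow-up.**
- Change: 2(1 − r)
- Baseline-adjusted: 1 − r²
- Ratio, adjusted to change: (1 + r)/2; the SE ratio is its square root
- Detectable effect: 2.80 × √(2 × variance/467)

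| r | Variance, change | Variance, adjusted | SE ratio | Detectable SD, change | Detectable SD, adjusted | Power for 0.2 SD, change / adjusted |
|---|---|---|---|---|---|---|
| 0.3 | 1.40 | 0.91 | 0.806 | 0.217 | 0.175 | 73% / 89% |
| 0.5 | 1.00 | 0.75 | 0.866 | 0.183 | 0.159 | 86% / 94% |
| 0.7 | 0.60 | 0.51 | 0.922 | 0.142 | 0.131 | 97.6% / 99.0% |
| 0.8 | 0.40 | 0.36 | 0.949 | 0.116 | 0.110 | 99.8% / 99.9% |

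In participants, 1,400 × (1 + r)/2 gives the number who, analysed with adjustment, match 1,400 analysed as changes: 910, 1,050, 1,190 and 1,260 for the four rows.

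**Mean of the three follow-ups**, with the same r between all pairs of occasions. The variance of the mean is (1 + 2r)/3. The change from baseline adds 1 − 2r to this; adjustment subtracts r². At r = 0.5 these are 0.667 and 0.417, an SE ratio of 0.79. The ratio is 0.69 at r = 0.3, 0.88 at 0.7 and 0.92 at 0.8.

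**Simulation.** 1,500 trials of 1,400 were simulated per setting, with five cities, 55% lower-educated (1,100/2,000), a true effect of 0.2 SD, and education correlated 0.1 or 0.2 with intake.
- Both analyses averaged 0.198 to 0.202.
- The empirical SE fell from 0.064–0.066 to 0.056–0.057 at r = 0.5, and from 0.049–0.050 to 0.046 at r = 0.7.
- Adding education after baseline moved the SE by no more than about 0.2%.
- Change and adjusted estimates from the same trial correlated 0.86 to 0.92.

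**Incomplete follow-up.** At the planned loss, 90% reach T1 and 0.9³ = 72.9% reach T3. If only people with all waves were analysed, 90 − 72.9 = 17.1% would have given at least T1 and been left out.

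**The case against.** The strongest reply is that the article is a condensed account and the model it describes is not pinned down. Repeated measures analysis could mean a likelihood mixed model with T0 among the outcomes. If its T0 means were constrained equal, it would already be about as efficient as baseline adjustment. That is fair, and it is why the fix is a clarification. It does not dispose of the point. With complete data, a mixed model with T0 as an outcome and free group-by-time means returns exactly the difference in mean changes. The gain needs the constraint or the covariate, and the section mentions neither.

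Second, the size depends on an r that the article does not give. This stands. Above 0.8 the gain is below about 5%, and for an assumed effect of 0.2 SD the change analysis already exceeds 80% power at r = 0.5 and above.

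A reader might also infer more than the text supports:
- **City is the only covariate.** It is the only one named; others are not excluded.
- **Adjusting for education sharpens the estimate.** It adds almost nothing once baseline is in the model.
- **27% of participants will be discarded** (100 − 72.9). This needs a completer analysis, which is stated nowhere; inflating recruitment for drop-out does not define an analysis set. Even then, only those with some follow-up, about 17%, have data to recover.
- **The two analyses give the same answer.** They share an expected effect under randomisation, but estimates in one trial differ, and with missing data complete-case and likelihood results can diverge further.
- **The change comparison is biased.** Under randomisation it is not.

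**Conclusion.** The point holds as an efficiency improvement, not as an error. The stated contrast is a difference in changes, and no adjustment for baseline intake is described. Adjustment would cut the single-follow-up SE by about 19%, 13%, 8% or 5% at r = 0.3, 0.5, 0.7 or 0.8, with a larger cut for the average of the three follow-ups. These figures rest on an assumed r, equal variances, equal allocation and complete data. The loss of about 17% of participants with usable follow-up applies only if a classical complete-case analysis is meant, which the article leaves open.

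**What to change.** State in Statistical analyses that the primary repeated measures model for T1 to T3 includes baseline intake of the behaviour concerned, with a baseline by time term, as a covariate. Equivalently, keep T0 as an outcome and constrain its mean to be equal across the three groups. Keep city in the model. Say that it is fitted by likelihood, so that every randomised participant with at least one follow-up contributes.

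Education may be added because the plan anticipates potentially higher drop-out among the lower-educated, which makes the missing-data assumption more credible; precision is not the reason.

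The cost is wording only. Baseline intake is measured before allocation, and the planned subgroup and interaction analyses already need baseline intake and education.
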